### **4.2. Adherence and protocol deviations**

Major protocol deviations are defined as instances where participants are not eligible, have not been randomized and blinded, have not completed all four follow-ups, or exhibit significant deviations from the prescribed time windows, specifically exceeding four weeks.

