### **Methods**

GLITTERS is a multicenter, double-blinded, randomized, and placebo-controlled clinical trial among knee OA patients with both Hoffa-synovitis and effusion-synovitis. Sixty participants will be allocated randomly and equally to either the glucocorticoid group or the control group. Each group will receive an injection of glucocorticoid or saline into the IPFP with an intra-articular hyaluronic acid injection as a background treatment at baseline, and be followed 4, 8, and 12 weeks. Primary outcomes will be changes in knee pain on a visual analogue scale and effusion-synovitis volume measured on magnetic resonance imaging (MRI). Secondary outcomes will be changes in the total score of Western Ontario and McMaster Universities Osteoarthritis Index score, MRI-detected Hoffa-synovitis score, quality of life, pain medication use, IPFP

volume, and the incidence of adverse reactions. Data analyses based on the intention-to-treat principle will include mixed-effects regressions, Wilcoxon rank-sum tests, and chi-square tests (or Fisher's exact test).

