## Outcome measures

An overview of the data collection is listed in Table 1. All questionnaires (VAS, WOMAC, four-dimensional Assessment of Quality of Life: AQoL-4D, and nine-items Patient Health Questionnaire: PHQ-9) and queries about pain medication use and the use of medication & supplements will be applied at baseline, 4, 8, and 12 weeks follow-ups. MRI assessments including effusion-synovitis volume, Hoffa-synovitis score, tibiofemoral bone marrow lesion maximum size, tibiofemoral cartilage defects, and IPFP volume will be examined at baseline and 12 weeks follow-up. Other measures including demographic data, clinical evaluation and history collection, ultrasonographic examination in the study knee, and effusion-synovitis score assessed by MRI will be recorded at baseline/screening only.

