## Questionnaires and queries

The VAS (100 mm visual analog scale) will be used to assess knee pain using the standard question: “On this line, how would you rate your knee pain in the last week?”. A higher score indicates a higher level of pain severity.

The WOMAC requires patients to rate their pain (five items), stiffness (two items), and functional dysfunction (17 items) in the last week. Each item is a 100-mm visual analog scale. The WOMAC score is calculated by summing the score of each

item with every 1 mm representing one point. A higher WOMAC score indicates a more severe OA symptom. When more than five items are not completed, the WOMAC score would be regarded as missing data. Otherwise, the WOMAC score would be calculated by averaging the remaining score and then multiplying by 24.

The AQL-4D will be used to assess the quality of life in the last week. It comprises four dimensions of independent living, social relationships, psychological well-being, and physical senses. Each dimension has three items with four response categories ranging from 0-3. The total AQL-4D score ranges from 0-36, and a higher score indicates a lower quality of life.

The PHQ-9 will be used to assess the depression in the last two weeks. It comprises nine items with four response categories scored from 0-3. The total PHQ-9 score ranges from 0-27, and a higher score indicates a more severe depression level.

Queries about medications and supplement use will also be recorded at baseline and each follow-up. Adverse events and reactions will be recorded at each follow-up. Pain medication use would be determined by the researchers from the records of medication use. Adverse events are defined as any untoward event occurring during the trial, regardless of its relation to treatment, and they need to be reported spontaneously when they occur. Details of the adverse event will be recorded and whether it is an adverse reaction will be determined.

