## Statistical plan

Baseline characteristics will be displayed in descriptive statistics according to the data type. Continuous variables with normal distribution will be displayed by means and standards deviation. Continuous variables with non-normal distribution will be displayed by median and interquartile range. Category variables will be displayed by proportion.

The intention-to-treat analysis will be the primary analyses method. The per-protocol analysis will be the second analyses method where the per-protocol population is defined as participants completed four follow-ups without major protocol deviations. There is no interim analysis in this research. Missing data due to dropout and nonresponses will be addressed using multiple imputations with chain equations. For each treatment group, imputations will be performed separately based on the baseline characteristics and the non-missing values at other time points of the missing variables with the assumption of data missing at random. Imputations will be performed separately for each treatment group and each outcome using baseline variables of age, sex, BMI, and study site and non-missing values of the outcomes at baseline and each follow-up with the assumption of data missing at random.

Mixed-effects regression models will be used to calculate treatment group differences with continuous measures. In the models, fixed effects will be follow-up time, baseline covariates (including age, sex, BMI, baseline value of the corresponding outcome), treatment, and interactions between follow-up time and baseline covariates and treatment. Study site and individual participant identification will be treated as the random intercepts and follow-up time as the random slop in the models. The overall treatment group differences will be calculated by the linear combination of the estimated coefficients. Wilcoxon rank-sum test will be used to analyze the difference in pain medication use between the treatment and placebo groups. Pain medication use will be classified as commenced/increased, unchanged, or discontinued/decreased. The chi-square test or Fisher's exact test will be used to compare the incidence of adverse reactions between the two treatment groups, and the number of adverse reactions will

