### **6.2. Analysis methods**

Baseline characteristics will be displayed in descriptive statistics according to the data type. Continuous variables with normal distribution will be displayed by means and standards deviation. Continuous variables with non-normal distribution will be displayed by median and interquartile range. Category variables will be displayed by proportion.

The intention-to-treat analysis will be the primary analyses method. The per-protocol analysis will be the second analyses method where the per-protocol population is defined as participants completed four follow-ups without major protocol deviations. There is no interim analysis in this research. Mixed-effects regression models will be used to calculate treatment group differences with continuous measures. In the models, fixed effects will be follow-up time, baseline covariates (including age, sex, BMI, baseline value of the corresponding outcome), treatment, and interactions between follow-up time and baseline covariates and treatment. Study site and individual participant identification will be treated as the random intercepts and follow-up time as the random slop in the models. The overall treatment group differences will be calculated by the linear combination of the estimated coefficients. Wilcoxon rank-sum test will be used to analyse the difference in pain medication use between the treatment and placebo groups. Pain medication use will be classified as commenced/increased, unchanged, or discontinued/decreased. The chi-square test or Fisher's exact test will be used to compare the incidence of adverse reactions between the two treatment groups, and the number of adverse reactions will be reported as the number of participants reporting at least one adverse reaction.

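### The per-protocol rule asks for four completed follow-ups where three are scheduled, tolerates timing errors as long as the visit interval, and does not require that the assigned injections were given

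*Combined protocol and SAP*

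**What the plan says.** Intention-to-treat is the primary analysis and per-protocol the second (Protocol, Statistical plan; SAP 6.2). The SAP states that "the per-protocol population is defined as participants completed four follow-ups without major protocol deviations". The protocol uses the same condition: "participants completed four follow-ups without major protocol deviations".

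SAP 4.2, headed as covering adherence and deviations, supplies the definition of a major deviation. It has four limbs: not eligible; not randomised and blinded; follow-up incomplete; or badly timed. The last two read "have not completed all four follow-ups, or exhibit significant deviations from the prescribed time windows, specifically exceeding four weeks".

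On the schedule, the protocol abstract says that participants will "be followed 4, 8, and 12 weeks". Table 1 has one screening/baseline column and three later columns, for weeks 4, 8 and 12. SAP 5.2 classes participants who do not return within 16 weeks as lost to follow-up. Under the protocol's Intervention section, treatment is two injections at baseline: glucocorticoid or saline into the fat pad, then intra-articular hyaluronic acid.

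**The concern.** A per-protocol set is meant to show the effect in participants who were treated and assessed as planned. Three features of this rule work against that.

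- The required number of follow-ups does not match the schedule, so membership depends on how a reader counts.
- The tolerated timing error is as long as the gap between visits, so the rule does not tie an assessment to one visit.
- The list does not ask whether the assigned treatment was given.

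If these are left open, the membership of a second analysis in a 60-person trial would have to be settled by interpretation once data are in hand. Timing matters here because the VAS asks about pain over the last week, so a score describes the date on which it was completed. Drift is also plausible: the week-4 and week-8 questionnaires are completed at home and sent back (Table 1 footnote).

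**Working it through.** **Expected size.** The documents give no figure for the per-protocol set. The nearest is the sample size, which reproduces: 2 × [(1.96 + 0.842) × 24.2 / 19.9]² = 23.22, rounded up to 24 per group, and 24 / 0.80 = 30 per group. It serves below only as a benchmark.

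**Count of follow-ups.** Required: 4 (Protocol, Statistical plan; SAP 4.2; SAP 6.2). Scheduled after baseline: 3 (abstract; Table 1).

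- *Literal reading.* 3 < 4 for everyone, so 0 of 60 qualify.
- *Baseline counted as the fourth.* The rule can be met. If the planned 20% loss were the only loss, 30 × 0.80 = 24 per group, or 48 of 60, would qualify. That is an assumption, not a forecast.

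The text is mixed on which reading applies. For the second: questionnaires "will be applied at baseline, 4, 8, and 12 weeks follow-ups", and Table 1 has four data columns. Against it: medication queries "will also be recorded at baseline and each follow-up", which names baseline separately. Likewise "Adverse events and reactions will be recorded at each follow-up", and Table 1 ticks these only at weeks 4, 8 and 12. The imputation text in the protocol's Statistical plan also separates baseline from each follow-up.

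**Timing.** Inputs: visits at weeks 4, 8 and 12 (days 28, 56 and 84), with a deviation major only beyond 4 weeks (28 days). The supplied text does not state the prescribed windows, so I measure from nominal dates. The 16-week limit in SAP 5.2 fits this, since 12 + 4 = 16.

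| Visit | Tolerated range | Part nearer to another visit |
|---|---|---|
| Week 4 | weeks 0-8 (days 0-56) | after week 6 |
| Week 8 | weeks 4-12 (days 28-84) | before week 6 or after week 10 |
| Week 12 | weeks 8-16 (days 56-112) | before week 10 |

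Adjacent ranges overlap by 8 − 4 = 4 weeks and 12 − 8 = 4 weeks. Days 28 to 84, which is 57 of the 113 days from day 0 to day 112, lie in at least two ranges. Day 56 lies in all three. If the four weeks run from the edge of a window of ±w weeks, the tolerance becomes 4 + w and the overlap grows.

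With a limit of t weeks (t at least 2), adjacent ranges overlap by 2t − 4 weeks: 4 at t = 4, 2 at t = 3, and 0 at t = 2. At exactly t = 2 they still share days 42 and 70. Only t < 2 separates them. In whole days, ±13 gives days 15-41, 43-69 and 71-97.

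**Treatment received.** Take a participant who was eligible, randomised and blinded, attended every assessment on time, but did not get the assigned injections. None of the four limbs of SAP 4.2 applies, so that participant stays in the per-protocol set.

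**The case against.** The best reply is that four plainly means the four assessments, so an empty set is a literalism. I accept that as the likely intent. It does not remove the defect: the same number stands in three places across two documents, and other sections keep baseline apart from the follow-ups.

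A second reply is that tolerating drift does not cause misassignment. Data are entered after each follow-up (Protocol, Data management), so a late form can keep its visit label, and a participant who completes visits in order cannot have the week-4 form at week 8 and the week-8 form at week 4. Effusion-synovitis volume has a single post-baseline MRI, so it cannot be confused with another visit. All of this stands. What remains is that the rule permits assessments nearer to another visit, and permits the single MRI anywhere in an eight-week span.

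Third, treatment is one baseline session, so failures of receipt should be few. That is fair, but it makes the criterion cheap to add, not unnecessary.

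A reader might also infer that treatments barred at entry, such as NSAIDs, should count as deviations if used later. The documents do not support this. Exclusion criterion 10 concerns current use at entry, and no section supplied bars these drugs afterwards. Pain medication use is a secondary outcome, so removing participants who start analgesics would select on a post-randomisation outcome that treatment is expected to change. If the injection works, more placebo participants would be removed.

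**Conclusion.** The rule needs correcting on three counts. The follow-up count contradicts the schedule. The timing limit equals the visit spacing, so that tolerated ranges overlap by four weeks and the week-12 primary outcomes can fall anywhere from week 8 to week 16. Receipt of the assigned injections is not required. The second and third hold whichever way the follow-ups are counted.

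The size of the first depends on the reading: 0 of 60 if literal, and a usable set if baseline is counted. The timing ranges assume that deviation is measured from the nominal date.

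Stronger statements would go too far. The documents do not show that the set will be empty in practice, or that visits will be mixed up; they show that the rule as worded allows the first reading and does not prevent the second. Nor does the point reach the main result: intention-to-treat is primary, its population does not depend on this rule, and no decision rule is attached to the per-protocol analysis.

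**What to change.** Make these changes before either step of the two-step unblinding, in the protocol's Statistical plan and in SAP 4.2 and 6.2:

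1. Replace the requirement for four follow-ups with completion of baseline and all three follow-ups (4, 8 and 12 weeks).
2. Set the per-protocol timing limit at less than 2 weeks either side of the nominal date (for example, at most 13 days), and say that it is measured from that date. A limit of exactly 2 weeks would leave shared boundary days. This governs membership of the analysis set only; it does not change when participants are seen or the 16-week loss-to-follow-up limit.
3. Add non-receipt of the assigned baseline injections to the list of major deviations.
4. Do not add NSAID or other analgesic use during follow-up to that list.

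The cost is wording, plus a check that receipt of both injections is recorded for each participant; Table 1 has no row for it. The downside is a smaller per-protocol set. The documents give no expected visit drift or non-receipt rate, so the loss cannot be estimated. Participants removed from this set stay in the intention-to-treat analysis.

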## **5. Trial population**

### **5.1. Eligibility**

- Inclusion criteria:

- 1) Diagnosed with symptomatic knee OA according to American College of Rheumatology criteria;
- 2) Age > 45 years;
- 3) Have knee pain for more than six months and the pain assessed by VAS (100 mm)  $\geq 40$  mm in last week;
- 4) Ultrasonography showed obvious synovitis (over about 10 ml) with effusion in the knee joint;
- 5) Both MRI-assessed Hoffa-synovitis score (MRI Osteoarthritis Knee Score, MOAKS method) and effusion-synovitis score (MOAKS method)  $\geq 1$ , and their total score  $\geq 3$ ;
- 6) Being able to listen, speak, read and understand Chinese, capable of understanding the study requirements and cooperating with the researchers during the study, and providing written informed consent.

- Exclusion criteria

- 1) Allergy to glucocorticoids;
- 2) Knee joint injection of glucocorticoid or hyaluronic acid within the past six months;

- 3) Severe trauma or arthroscopy in the knee within the past six months;
- 4) Planned hip or knee surgery (including arthroscopy, arthroplasty, and other open joint surgeries) in the next six months;
- 5) Contraindication to having MRI (e.g., implanted pacemaker, artificial metal valve or cornea, aneurysm clipping surgery, arterial dissection, metal foreign bodies in the eyeball, claustrophobia);
- 6) Presence of other arthritis, such as rheumatoid arthritis and psoriatic arthritis;
- 7) Other condition that is more painful than their knee OA;
- 8) Malignant tumors or other life-threatening diseases;
- 9) Infection, diabetes, coagulopathy, osteonecrosis, or gastric/duodenal ulcer within the past 12 months;
- 10) Current use of oral corticosteroids, nonsteroidal anti-inflammatory drugs, or immunosuppressive medication;
- 11) Pregnancy or lactating female;
- 12) Use any investigational drugs or devices in the recent 30 days.

Note: When both knees of the participants meet the eligibility criteria, the knee with more severe VAS pain will be selected as the study knee.

## **5.2. Withdraw/follow-up**

The participants are allowed to withdraw at any time throughout the study. If the participants withdraw from the study before the end of the trial, they are asked to have data collected including MRI assessment. The reason and date of the withdrawal will be recorded and the data before the withdrawal will be asked to retain.

In instances where participants experience a serious adverse event leading to their unblinding, such circumstances will be considered equivalent to withdrawal from the trial. Participants who cannot be reached or fail to return within a 16-week timeframe will be classified as lost to follow-up.

## **5.3. Baseline patient characteristics**

Baseline factors such as demographic data (gender, birth date, height, weight, and study site), questionnaire responses (VAS, WOMAC, AQL-4D, PHQ-9), and information on medication and supplement usage will be collected prior to the intervention. These will be analysed by randomized treatment arm to compare the groups. However, any differences in baseline characteristics will be attributed to chance rather than bias.

## **6. Analysis**

### **6.1. Outcome definition**

- Primary outcomes: changes in knee pain as assessed by the VAS and effusion-synovitis volume measured on MRI.
- Secondary outcomes: changes in the total score of WOMAC, MRI-detected Hoffa-synovitis score, quality of life measured using AQoL-4D, pain medication use, IPFP volume, and the incidence of adverse reactions.

### **6.2. Analysis methods**

Baseline characteristics will be displayed in descriptive statistics according to the data type. Continuous variables with normal distribution will be displayed by means and standards deviation. Continuous variables with non-normal distribution will be displayed by median and interquartile range. Category variables will be displayed by proportion.

The intention-to-treat analysis will be the primary analyses method. The per-protocol analysis will be the second analyses method where the per-protocol population is defined as participants completed four follow-ups without major protocol deviations. There is no interim analysis in this research. Mixed-effects regression models will be used to calculate treatment group differences with continuous measures. In the models, fixed effects will be follow-up time, baseline covariates (including age, sex, BMI, baseline value of the corresponding outcome), treatment, and interactions between follow-up time and baseline covariates and treatment. Study site and individual participant identification will be treated as the random intercepts and follow-up time as the random slop in the models. The overall treatment group differences will be calculated by the linear combination of the estimated coefficients. Wilcoxon rank-sum test will be used to analyse the difference in pain medication use between the treatment and placebo groups. Pain medication use will be classified as commenced/increased, unchanged, or discontinued/decreased. The chi-square test or Fisher's exact test will be used to compare the incidence of adverse reactions between the two treatment groups, and the number of adverse reactions will be reported as the number of participants reporting at least one adverse reaction.

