### **3. Study methods**

#### **3.1. Trial design**

GLucocorticoid injections into InfrapaTellar faT pad in patients with knee osteoarthritis (GLITTERS) is a multicentre, randomized, double-blind, placebo-controlled trial over 12 weeks. Participant recruitment is conducted across four centres: Zhujiang Hospital of Southern Medical University, the Sixth Affiliated Hospital of Sun Yat-sen University, the Third Affiliated Hospital of Sun Yat-sen University, and Beihai People's Hospital. This study will use competitive enrolment.

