#### **3.2. Randomization and blinding**

Using block randomization in block size of four, eligible participants in each centre will be assigned to the treatment or placebo group with a 1:1 allocation rate based on computer-generated random numbers. A staff member who is not involved in this trial will pack the drugs with a random number indicated on each of the packages. Allocation concealment will be ensured and Allocation results will be not revealed until the completion of final data analyses. Double-blind (participants & researchers including outcome assessors and statisticians) design will be applied in this trial. Because of the different appearance of the injection drugs, the physical therapists for the injections are not blinded, and they will not be involved in other processes of this trial. During the period of preparing and injecting the drug, participants will be out of sight of the injection drugs. Unblinding will be conducted after all the data analyses are obtained. Emergency unblinding will be permissible when a serious adverse event (AE) happens, and patients who are unblinded will be withdrawn from the trial.

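### Randomisation is blocked within centre, but the tests for pain medication use and adverse reactions pool the centres; if centres differ, these tests are conservative and lose some power.

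*Combined protocol and SAP*

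**What the plan says.** SAP 3.2: "Using block randomization in block size of four, eligible participants in each centre will be assigned to the treatment or placebo group". The protocol's Randomization and blinding section says the same. SAP 3.1 adds that "Participant recruitment is conducted across four centres" and that "This study will use competitive enrolment", so centre sizes are not fixed in advance.

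SAP 6.2 and the protocol's Statistical plan make study site a random intercept in the mixed models for continuous outcomes. Site is also a predictor in the imputation (SAP 6.3 and the protocol's Statistical plan).

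Two secondary outcomes are handled differently. For medication use SAP 6.2 states "Wilcoxon rank-sum test will be used to analyse the difference in pain medication use between the treatment and placebo groups", and the protocol's Statistical plan says the same. The variable has three ordered levels: "Pain medication use will be classified as commenced/increased, unchanged, or discontinued/decreased". For safety, "The chi-square test or Fisher's exact test will be used to compare the incidence of adverse reactions between the two treatment groups". Neither document stratifies or adjusts these tests by site.

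**The concern.** Blocking within centre makes the arms nearly equal in size at each hospital, so differences between hospitals largely cancel out of the treatment comparison. A pooled rank or chi-square test does not use this. Its null variance still contains the between-centre variation, so the standard error is too large whenever centres differ on the outcome.

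At stake is efficiency in two secondary comparisons. For medication use, a real effect may be missed. For adverse reactions, a conservative test makes a real difference in harm somewhat easier to miss. The plan already respects the stratifier in its mixed models, so these two tests are the exception.

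**Working it through.** **The plan's own figure.** SAP 3.3 gives a sample size only for VAS pain: 2 × [(1.96 + 0.842) × 24.2 / 19.9]² = 23.22, rounded up to 24 per group. Then 24 / 0.80 = 30 per group, or 60 in total. This reproduces. The plan gives no power for the two tests at issue, so the check has to assume the remaining inputs.

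**Inputs from the documents.** 60 participants, four centres, 1:1 blocks of four within centre, three ordered medication categories, two-sided 0.05.

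**Assumed inputs.** Centres of 24/16/12/8, a treatment log odds ratio of 1.3 (odds ratio about 3.7), and normal centre effects with SD σ on the logit scale.

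**Analytic check of type I error.** If a share ρ of the outcome variance lies between centres, the pooled z statistic has variance of about 1 − ρ under blocked allocation. The true level is then about 2[1 − Φ(1.96/√(1 − ρ))]. With centre shares w, k = 1 − Σw² = 1 − (0.400² + 0.267² + 0.200² + 0.133²) = 0.711. On the latent logistic scale, ρ = kσ²/(kσ² + π²/3), with π²/3 = 3.29.

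| σ | ρ | 1.96/√(1 − ρ) | approximate true level |
|---|---|---|---|
| 0.3 | 0.064/3.354 = 0.019 | 1.98 | 4.8% |
| 0.6 | 0.256/3.546 = 0.072 | 2.03 | 4.2% |
| 1.0 | 0.711/4.001 = 0.178 | 2.16 | 3.1% |
| 1.5 | 1.600/4.890 = 0.327 | 2.39 | 1.7% |

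**Simulation of the Wilcoxon test, same setting.**

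| σ | pooled type I error | pooled power | stratified power | loss |
|---|---|---|---|---|
| 0.3 | about 5% | 0.74 | 0.74 | none |
| 0.6 | about 4% | 0.71 | 0.73 | 2 points |
| 1.0 | about 3% | 0.64 | 0.71 | 7 points |
| 1.5 | about 2% | 0.51 | 0.64 | 13 points |

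The van Elteren test stays at about 5% throughout. The simulated levels agree with the analytic ones.

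**Adverse reactions.** Assumed: control rate 20%, odds ratio 5, four centres of 15, and fixed centre shifts on the logit scale, with 10,000 simulated trials per setting. Moderate shifts are ±0.2 and ±0.7 (root mean square √0.265 = 0.51). Large shifts are ±0.5 and ±1.5 (√1.25 = 1.12).

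| centre shifts | chi-square type I error | chi-square power | Mantel-Haenszel power |
|---|---|---|---|
| none | 0.049 | 0.84 | 0.84 |
| moderate | 0.048 | 0.80 | 0.82 |
| large | 0.031 | 0.66 | 0.74 |

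With centres of 30/14/10/6 and large shifts, power is 0.58 for chi-square and 0.66 for Mantel-Haenszel. Fisher's exact test already has a type I error of 0.029 with no centre differences and equal centres. That part comes from the test's discreteness, and stratifying would not remove it.

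**Cost of stratifying.** With centres of 40/12/5/3 (assumed), 20% loss, no imputation and no centre differences, Wilcoxon power is 0.637 stratified and 0.658 pooled, a cost of about 2 points. At σ = 0.6 the same layout gives 0.612 against 0.606, a small gain.

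**The case against.** The strongest reply is that nothing in the documents shows that centres differ on these outcomes. That stands. A reader might infer that medication use follows local prescribing and is therefore the outcome most likely to vary by hospital. No section says so. The analysed variable is a category of change from baseline rather than a level of use, and current users of nonsteroidal anti-inflammatory drugs are excluded at every centre (SAP 5.1). Both could narrow the differences.

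A reader might also infer that these tests run below 5% as a matter of fact. The documents do not support that. It holds only if centres differ, and at an SD of 0.3 there is nothing to see.

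The pooled tests also remain valid, since the error is towards caution. The sample size section sets no power target for either outcome, and both primary outcomes are modelled with site. All of this stands and keeps the point minor.

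Stratifying is not entirely free either. Competitive enrolment may leave tiny centres, and a centre with one arm only contributes nothing. This qualifies the recommendation but does not reverse it: with centres of 24/16/12/8 and 20% loss, the stratified Wilcoxon still gains about 3 points at SD 0.6 and about 5 at 1.0. The exact stratified test for adverse reactions was not simulated.

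**Conclusion.** The point holds in conditional form. Allocation is blocked by centre and the mixed models include site, but the Wilcoxon and chi-square or Fisher tests pool the centres. If centres differ, those tests are conservative and lose power. For the Wilcoxon test the loss runs from nil to about 13 points over the assumed range of centre SDs from 0.3 to 1.5. The chi-square loss is about 2 points for moderate and about 8 for large shifts with equal centres. All of these sizes rest on assumed centre sizes, effects and centre differences.

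Two stronger readings are not supported. The mismatch does not create false positives, and it does not touch the primary outcomes. SAP 6.2 also names no visit for the medication comparison, although use is recorded at baseline and weeks 4, 8 and 12. That is a separate missing detail and no part of this argument.

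**What to change.** In SAP 6.2 and the protocol's Statistical plan, replace the Wilcoxon rank-sum test with the van Elteren test stratified by study site. For adverse reactions, replace the chi-square or Fisher test with a Mantel-Haenszel test stratified by site, using the exact form where cells are sparse. State beforehand how a very small or one-arm centre will be handled, and how the stratified statistic will be combined across imputed data sets. The plan does not state the latter for the pooled Wilcoxon test either.

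The cost is a line or two of text. The methods are standard in SAS and R, which SAP 6.4 names, and no new data are needed. The statistical price is up to about 2 points of power if centres turn out not to differ, 20% are lost and enrolment is very uneven.
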